### Study endpoints

The primary endpoint is the occurrence of PES within the first 48 h after extubation. Secondary endpoints include oxygen therapy after extubation, respiratory support requirements, reintubation secondary to PES within 48 h after extubation, and adverse effects (glycemic change, gastrointestinal bleeding or neuropsychiatric events). Clinical assessments will be done at 5, 15, 30, and 60 min, and then at 3, 6, 12, 24, 36, and 48 h after extubation. Hospital length of stay and hospital mortality will also serve as secondary endpoints (see Fig. 2 for study flow chart).

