### Data collection and management

For each participant, anthropometric data (gender, age, body mass index (BMI)) and baseline characteristics such as GCS score, Acute Physiology and Chronic Health II (APACHE II) score, vital signs (blood pressure, heart rate, respiratory rate, blood oxygen saturation and temperature), and arterial blood gases (ABGs) will be recorded as long as the patients are in-hospital. Arterial blood oxygen saturation (SaO_2_), as well as end tidal carbon dioxide (PETCO_2_) if available, will be continuously recorded. In order not to cause unnecessary pain to patients, ABGs will be collected when deemed clinically necessary during follow-up, while other baseline characteristics will be recorded at set times.

We will also record incidence of the following for each enrolled patient:
PES, defined as a presence of an audible high-pitched sound with respirationOxygen therapy after extubation (e.g., nasal catheter, reservoir mask or venturi mask)Requiring a respiratory support, as defined by:
Presence of respiratory acidosis (an arterial pH of less than 7.35 with a partial pressure of arterial carbon dioxide of more than 45 mmHg)Clinical signs of increased respiratory effort (use of accessory muscles, intercostal retractions, or paradoxical motion of the abdomen)Respiratory rate > 30 breaths/min for two consecutive hoursHypoxemia (SaO_2_ of < 90% with an FiO_2_ > 50%)Reintubation secondary to PESAdverse effects due to corticosteroidsHospital length of stayHospital mortality.

Clinical data will be collected locally via the Research Electronic Data Capture (REDCap) system, an Internet-based electronic case report form (CRF). The research coordinators at each hospital will form a steering committee, which provides training and reviews study processes, to improve adherence to the protocol and resolve problems. In addition, they will regularly audit CRFs and contact responsible medical staff members every 3 months to ensure data quality and accuracy. All data use will be limited to study analysis only, and no individuals’ personal information will be published. Data confidentiality will be under the supervision of the study coordinators and the Ethics Committee of Peking Union Medical College Hospital.

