### Statistical methods

The primary endpoint will be analyzed on an intention-to-treat basis, regardless of whether subjects complete their originally allocated treatment study protocol. Any reasons for protocol violations will be recorded and described. All *p* values will be two-tailed, and significance will be a *p* value < 0.05. Data will be presented as frequencies and percentages for categorical variables. Continuous variables will be expressed as means with standard deviations (when normally distributed) or as medians with interquartile ranges (for skewed distribution). Student’s *t* test (normal distribution) or Mann-Whitney *U* test (skewed distribution) will be used for group comparisons. Categorical variables will be compared using Pearson’s chi-squared test or Fisher’s exact test as appropriate. Statistical uncertainty will be expressed in terms of a relative risk and 95% confidence intervals.

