There are some limitations to this study. First, our study mainly focuses on the initial conditions of intubated patients in the ED. Esteban [27] found that survival in patients receiving mechanical ventilation depended on not only each patient’s condition when initiating mechanical ventilation, but also on how the condition changes and complications develop subsequently. Although we will attempt to control for complications, these may still affect the outcomes. Second, we include extubation failure as one of our secondary outcomes, but it is important to mention that other factors such as pulmonary edema also lead to extubation failure and could be alleviated by corticosteroids as well. Third, there is currently no universally acknowledged extubation standard, so extubation decision made mainly on clinical experience.

This will be the first study looking at the prophylactic methylprednisolone for preventing PES in patients after an emergency intubation. As more patients spend longer periods of time in the ED, it is important to understand the best method for minimizing the complications and maximizing ED patient safety during extubation.

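### Hospital mortality is compared only without adjustment although APACHE II is a recorded baseline variable: a valid analysis that forgoes a modest gain in precision

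*Protocol article*

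**What the plan says.** Under Study endpoints, the protocol article makes hospital mortality a secondary endpoint: "Hospital length of stay and hospital mortality will also serve as secondary endpoints".

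Under Statistical methods, the comparison for such an outcome is "Categorical variables will be compared using Pearson’s chi-squared test or Fisher’s exact test as appropriate", and "Statistical uncertainty will be expressed in terms of a relative risk and 95% confidence intervals". No covariate is named.

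Under Data collection and management, the variables recorded for each participant include "baseline characteristics such as GCS score, Acute Physiology and Chronic Health II (APACHE II) score". The legend of Fig. 1 also lists APACHE II under baseline variables. Randomization is stratified by sex and not by severity.

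The limitations in the Discussion cite earlier work in which "survival in patients receiving mechanical ventilation depended on not only each patient’s condition when initiating mechanical ventilation". The same sentence names the later clinical course as a second driver of survival.

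**The concern.** Patients enter after emergency intubation for reasons ranging from trauma to cardiac arrest, so their risk of death is likely to differ for reasons that one injection before extubation cannot change. A severity score is collected, the design does not stratify on it, and the stated analysis of deaths does not use it. When a baseline variable predicts the outcome, adjusting for it removes part of the outcome variance from the treatment comparison and needs no more patients. What is at stake is the width of the interval around the mortality effect. Prespecifying the adjustment also avoids an ad hoc one, chosen after unblinding because severity happens to look unbalanced.

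**Working it through.** **The plan's own figure.** The only sample size in the document is for post-extubation stridor: 30% against 10%, two-sided alpha 0.05, power 80%. The unpooled normal formula gives n = (0.3×0.7 + 0.1×0.9) × (1.960 + 0.842)² / 0.2² = 58.9, so 59 per group. Allowing for drop-out, 59/0.9 = 65.6, so 66 per group and 132 in total. The stated figures reproduce, and this point does not touch them. No figure is given for mortality.

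**Inputs for mortality.** From the document: 132 randomized, 66 per arm. Assumed, because the document gives neither: mortality m of 10%, 15% or 25%, and a standardised score x with logit p(x) linear in x and slope 0.5, 0.8 or 1.2 per SD. These slopes correspond to AUCs of about 0.64, 0.70–0.71 and 0.78–0.79.

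**Formulas.**
- Share of outcome variance explained: R² = Var{p(x)} / [m(1 − m)].
- Fall in the standard error of the marginal risk difference: 1 − √(1 − R²).
- Equivalent extra patients: 132 × R² / (1 − R²).

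| Mortality | Slope | R² | Fall in SE | Extra patients |
|---|---|---|---|---|
| 10% | 0.5 | 0.023 | 1.2% | 3 |
| 10% | 0.8 | 0.060 | 3.0% | 8 |
| 10% | 1.2 | 0.129 | 6.7% | 20 |
| 15% | 0.5 | 0.032 | 1.6% | 4 |
| 15% | 0.8 | 0.078 | 4.0% | 11 |
| 15% | 1.2 | 0.158 | 8.2% | 25 |
| 25% | 0.5 | 0.044 | 2.2% | 6 |
| 25% | 0.8 | 0.102 | 5.3% | 15 |
| 25% | 1.2 | 0.194 | 10.2% | 32 |

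Worked end points: 132 × 0.0231/0.9769 = 3.1 and 132 × 0.1936/0.8064 = 31.7.

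**Check by simulation.** There were 66 patients per arm, mortality was halved in the treated arm, and 1,500 trials were run per scenario. Runs with no deaths in an arm were dropped. The SD is that of the risk difference, crude or standardised from the adjusted logistic model. Power is for the Wald test of the arm coefficient.

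| Placebo mortality | AUC | SD crude | SD adjusted | Power crude | Power adjusted |
|---|---|---|---|---|---|
| 10% | 0.7 | 0.0436 | 0.0430 | 0.09 | 0.11 |
| 20% | 0.7 | 0.0605 | 0.0591 | 0.35 | 0.37 |
| 20% | 0.8 | 0.0621 | 0.0573 | 0.34 | 0.40 |
| 30% | 0.8 | 0.0737 | 0.0656 | 0.56 | 0.66 |

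The SD falls by 1.4%, 2.3%, 7.7% and 11.0%. The last row lies outside the range used for the conclusion and shows the most favourable corner. At an AUC of 0.6 the gain almost vanishes (20% mortality: 0.0598 against 0.0597).

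**Scale matters.** In a plain logistic model the standard error of the log odds ratio rises with adjustment (20% mortality, AUC 0.7: 0.519 to 0.545), because the conditional odds ratio is a different estimand. The gain appears once the model is standardised back to marginal risks.

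**The case against.** The strongest reply is that nothing here is wrong. A chi-squared or Fisher test with a relative risk is valid under 1:1 randomization, and its interval already allows for chance imbalance in severity. Mortality is an unpowered secondary endpoint, and covariate adjustment is often left to an analysis plan, which is not shown. All of that stands. The point survives only as a better use of data already collected, measured against the method the article does state.

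Three stronger readings are tempting, and the documents do not support them.

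- A reader might infer that chance imbalance in severity could dominate the mortality comparison. With R² between 2% and 19%, at least 81% of the outcome variance is unrelated to the score, and adjustment would not remove it.
- A reader might infer from the Discussion that the protocol rests survival on the initial condition. The cited sentence names the initial condition and the later course together. It supports baseline severity as one driver, but later complications arise after randomization and cannot be adjusted for in this way.
- A reader might call the gain free. It needs a model and standardisation. If mortality were the same in both arms, 10–20% would mean only about 13–26 deaths (132 × 0.10 and 132 × 0.20).

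Timing is a fair further objection. The mix of reasons for intubation describes patients earlier in their course. Allocation follows a passed spontaneous breathing trial and a failed cuff-leak test, so those randomized may be more alike and an early score less predictive. Fig. 1 is not shown, so the time of scoring cannot be confirmed. This pushes the gain towards the lower end of the range.

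**Conclusion.** The point holds as a minor efficiency suggestion. The stated mortality analysis is unbiased but leaves a modest gain in precision unused: about 1–10% off the standard error of the risk difference, or about 3–32 patients' worth of information. This rests on assumed mortality of 10–25%, an assumed AUC of about 0.64–0.78, and a score taken close enough to randomization to keep that AUC. It would not rescue the endpoint. At 10–20% placebo mortality, simulated power for even a halving of deaths stays at or below about 0.40 with or without adjustment. No conclusion on the primary endpoint is affected.

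**What to change.** Add a sentence to the analysis text: hospital mortality will be analysed by logistic regression on treatment arm and APACHE II, with predicted risks standardised over all randomized patients to give a marginal relative risk and a risk difference, each with a 95% confidence interval, and the crude comparison shown beside them. The relative risk keeps the plan's own effect measure.

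State that the APACHE II value is one obtained before randomization, and which one. This matters because the article has the listed measurements recorded during the hospital stay, so later values may also exist. State also that the crude result stands if an arm has no deaths. At 5% mortality in an arm of 66 the chance of that is 0.95^66 = 3.4%.

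The cost is wording only, with no new data and no more patients. The small downside is a model-based estimate from few deaths, which is why the crude result should stay visible.

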**Fig. 2 Fig2:**
[figure not shown]
Study flow chart

### Sample size calculation

We used a chi-squared statistical analysis of minimum sample size required to evaluate the effect of corticosteroids on our study outcomes. Cheng [10] showed that either a single or multiple doses of methylprednisolone 6 h before extubation reduced the incidence of PES compared to placebo (11.6%/7.1% vs 30.2%). Cheng [11] later reported that a single dose of methylprednisolone 4 h before extubation significantly reduced the incidence of PES from 39.4 to 15.8%. Other studies treating with prophylactic dexamethasone showed that it decreased the incidence of PES from 27.5–30.2 to 8.8–11.5% [12, 16]. We therefore anticipate an incidence of PES of 10% in the treatment group and 30% in the placebo group. With an 80% power to detect a difference and a two-sided alpha of 0.05, we anticipate needing 59 subjects in each group. Assuming a drop-out rate of 10%, we calculate a total minimum sample size of 132 subjects.

### Randomization and blinding

As female sex has been reported to be an independent risk factor for stridor and extubation failure [5, 7, 10, 17, 18], a gender-stratified block randomization will be performed in a 1:1 ratio. Within each stratum, a random block size of four will be used. After completion of the pre-extubation assessment and obtaining written informed consent, participants will be randomly assigned to either the intervention group or the control group. Staff not assigned to patient therapy or assessment will be responsible for injecting the intervention; thus, both patients and therapists involved will be blinded to treatment allocation. All analyses will be performed on an intention-to-treat basis.

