Ideally, patients at high risk for PES should be identified before extubation. The cuff-leak test (CLT), defined as the difference in the actual tidal volume before and after cuff deflation, has been proposed for this purpose [8, 9]. Previous studies described a cuff leak volume less than 110 ml or 24% of tidal volumes as insufficient [10–12], and evidence showed absent or insufficient cuff leak volume suggested an increased risk of PES and extubation failure [8]. Several studies showed the CLT has a good specificity but poor sensitivity, and the accuracy for predicting PES varied with different studies [13–15]. Moreover, the measured tidal volume could also be influenced by other factors such as system compliance or airflow resistance [13]. However, the CLT is still preferred as it has been showed to decrease the risk of PES and reintubation [9].

We conceived the present protocol in order to evaluate whether a single dose of methylprednisolone given over a set timeframe before extubation is effective in reducing the incidence of PES in patients who had been intubated on an emergency basis and were approaching extubation. We hope to answer this question through a multicenter, double-blind, randomized controlled trial.

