## Methods

### Trial design and setting

This is an investigator-initiated, multicenter, superiority, randomized controlled trial that will include 132 participants in intervention arm. Six large tertiary hospitals in China will be involved in this trial. This study was prospectively registered with Chictr.org.cn on February 29, 2020 (identifier: ChiCTR 2000030349). The Ethics Committee of Peking Union Medical College Hospital, Chinese Academy of Medical Science, and Peking Union Medical College in Beijing has approved the trial protocol. The schedule of enrollment, intervention, data collection, and assessment follows the Standardized Protocol Items: Recommendations for Interventional Trials (SPIRIT) guidelines (see Fig. 1 for checklist and Additional File 1 for more details).

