### Intervention, control, and observation groups

Once eligible patients successfully pass a spontaneous breathing trial (SBT), a CLT will be performed to evaluate their risk for developing PES. Patients who had a cuff-leak volume (CLV) less than 24% of vital volume will be included in the intervention arm, where they will be randomly allocated to either the corticosteroid group or the placebo group. The planned extubation will be implemented within 6 h after allocation. Patients in the corticosteroid group and placebo group will be treated with an intravenous injection of methylprednisolone 40 mg (corticosteroid) or an equivalent volume of isotonic saline (placebo) 4 h prior to extubation. Patients with a CLV > 24% of tidal volume will serve as a control group, where extubation will be performed within 2 h after CLT completion.

All other standard precautions or treatments will be implemented in all patients.

Precautions include gentle extubation to avoid laryngotracheal mucosal injury, strict endotracheal tube (EET) fixation to avoid repeated friction between the EET and laryngotracheal mucosa, and EET nursing to reduce contamination risk. Any treatments for PES will be applied in accordance with each patient’s condition, including oxygen therapy with inhaled corticosteroid for mild airway edema and intravenous administration of hydrocortisone (100 mg) for moderate airway edema. Non-invasive ventilation or re-intubation will be carried out as clinically indicated if the above treatments are ineffective.

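### One published block size of four, sex as the only stratum across six hospitals, and an unstratified primary test: the test stays valid, but predictability and precision could be improved at almost no cost

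*Protocol article*

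**What the plan says.** Under Randomization and blinding, the Protocol article states that "a gender-stratified block randomization will be performed in a 1:1 ratio" and then that "Within each stratum, a random block size of four will be used". Sex is chosen because it is reported as a risk factor for stridor and extubation failure. No other stratification factor is named.

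Trial design and setting says "Six large tertiary hospitals in China will be involved in this trial". The Background calls the study a "multicenter, double-blind, randomized controlled trial". The placebo is saline of equal volume, and patients and therapists are blinded because "Staff not assigned to patient therapy or assessment will be responsible for injecting the intervention". The article does not say whether those staff know the allocation, or whether the list is held centrally or at each hospital.

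For analysis, Statistical methods says "Categorical variables will be compared using Pearson’s chi-squared test or Fisher’s exact test as appropriate", with a relative risk and 95% confidence interval. It mentions neither sex nor hospital in that comparison.

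**The concern.** Three features invite a closer look.

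- **Block size.** The sentence gives one value, so the size does not vary. At most, *random* can describe the order of treatments within a block. The value is also in the public domain. Anyone who learns the earlier assignments in a stratum can work out how a block must end.
- **Hospital.** Stridor is defined as an audible high-pitched sound, so it is judged by ear at the bedside. The Discussion concedes that there is no agreed extubation standard, "so extubation decision made mainly on clinical experience". Hospital is therefore a plausible source of variation in the primary outcome, yet neither the list nor the test takes account of it.
- **Sex.** The list is balanced on sex because sex is thought prognostic, but the stated test then ignores it. The precision that the stratification could give is not used.

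At stake are the unpredictability of assignment, how comparable the arms look within each hospital, and the precision of a trial sized with little to spare.

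**Working it through.** **Inputs from the Protocol article:** blocks of 4; 1:1 allocation; two strata (sex); six hospitals; stridor in 10% versus 30%; 80% power; two-sided alpha 0.05; 59 per group; 10% drop-out; 132 in total.

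**Assumptions not in the documents:** 22 patients per hospital (132 / 6), or recruitment equal only on average, or moderately unequal; 40% women; hospital event rates spread from 10% to 50% for the validity check.

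**1. The plan's own figure.** Unpooled two-proportion formula: n = (1.96 + 0.8416)² × (0.3×0.7 + 0.1×0.9) / 0.2² = 7.849 × 0.30 / 0.04 = 58.87, so 59 per group. With drop-out, 59 / 0.9 = 65.6, so 66 per group and 132 in total. Both stated figures reproduce.

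**2. Predictability with a known block of four.** Take someone who knows every earlier allocation in the stratum. The six orderings of AABB contain this many positions fixed by what went before:

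- AABB 2, BBAA 2
- ABAB 1, ABBA 1, BABA 1, BAAB 1

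That is 8 of 6 × 4 = 24 positions, or one third. The best guess is right with probability 1/2, 2/3, 2/3 and 1 at positions 1 to 4, a mean of 2.833 / 4 = 70.8%.

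If sizes 4 and 6 are mixed at random, a best guesser who knows the mix and all earlier allocations is certain about 5% of the time and right about 69% of the time. Varying the size removes most of the certainty but little of the average guessing accuracy, so withholding the sizes matters too.

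If one list per sex is shared by all six hospitals, a hospital that knows only its own past allocations and guesses from their running balance is right about 52% of the time.

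**3. Balance within a hospital under sex-only stratification.** For one hospital with 22 of the 132 patients, treat the number X on active treatment as hypergeometric (132 patients, 66 active, 22 drawn). The arm difference is |2X − 22|.

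- P(difference ≥ 6) = P(X ≤ 8 or X ≥ 14) = 0.243
- P(difference ≥ 8) = P(X ≤ 7 or X ≥ 15) = 0.101

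Simulating the stated scheme with exactly 22 patients per hospital gives the same two values. It also shows at least one of the six hospitals differing by 8 or more in about 45% of trials. When hospital sizes vary at random, this falls to 37% (equal expected recruitment) or 34% (moderately unequal).

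**4. What stratifying the list by hospital would change** (simulation, equal expected recruitment, blocks of four):

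| | Sex only | Sex by hospital |
|---|---|---|
| Mean arm difference within a hospital | 3.4 | 1.0 |
| Mean of the largest hospital difference | 6.9 | 2.1 |
| Some hospital differs by 8 or more | 37% | 0% |
| Mean overall arm difference | 0.8 | 2.4 |

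Blocks of four cap the difference at 2 per stratum, hence 2 × 2 = 4 per hospital. Mixed blocks of 4 and 6 cap it at 3 per stratum and 6 per hospital.

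**5. Validity of the unadjusted test.** With hospital event rates spread from 10% to 50% and no treatment effect, the simulated type I error of the chi-squared test was 5.0%, against 5.1% with equal rates. Chance imbalance by hospital does not inflate it.

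**The case against.** The case for leaving the plan alone has real force.

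- **Blinding.** Therapists are blinded, the placebo matches in volume, and the injecting staff are kept out of therapy and assessment. Assignment follows the pre-extubation assessment and consent, and entry rests on a numeric cuff-leak threshold. For selection bias to arise, injecting staff would have to know every earlier allocation in the stratum and pass it on to those who enrol. This stands: a reader might infer that the sequence is simply guessable at enrolment, and the article does not support that. What remains is narrower. No masking of the injecting staff is described, and a fixed public block size helps anyone in that position.
- **The two harms need opposite set-ups.** With one shared list per sex, hospital balance is uncontrolled but a hospital guesses right only about 52% of the time. With lists held at each hospital, guessing is easier but blocks of four already keep hospitals nearly balanced. The article does not say which applies, so both harms cannot be claimed at full strength together.
- **Chance imbalance is not bias.** A reader might infer that site differences will be mixed into the treatment effect. Over repeated trials they are not, as step 5 shows. The cost is a possible chance imbalance in the one trial that is run, and some lost precision.
- **Hospital variation is inferred.** The article gives no between-hospital figures for stridor, and its remark on clinical experience does not say that practice differs by site.
- **Sex-only stratification is legitimate at this size.** Adding hospital makes 6 × 2 = 12 strata averaging 132 / 12 = 11 patients. This stands, and it is why stratifying the list by hospital is optional here.
- **An analysis plan may refine the test.** It may. But the article names the test for categorical outcomes, and that test leaves out the factor used in randomisation.

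**Conclusion.** The point holds as a modest design improvement. It is not a flaw that threatens validity. The article fixes one block size, mislabels it as random and publishes it. It stratifies by sex only across six hospitals and states a test that uses neither factor.

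The size of each cost:

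- **Predictability:** one third of assignments are certain, but only to someone who knows all earlier allocations in that stratum.
- **Hospital balance:** about a 10% chance that a given hospital differs by 8 or more between arms, assuming 22 patients each and a list shared across hospitals. The chance that some hospital does so is about 34% to 45%, depending on how recruitment is spread.
- **Precision:** some is lost. How much depends on how strongly sex and hospital predict stridor, which the article does not quantify.

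Type I error is unaffected, and the sample size of 132 needs no change on this account.

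**What to change.** Before the first patient is randomised:

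1. Replace the single block size with randomly varying sizes (for example 4 and 6). Keep the actual sizes in a restricted document withheld from all site staff, including those who give the injections. In the protocol, say only that sizes vary and are concealed, and state whether the list is central.
2. State that stridor will be compared with a test and relative risk stratified by or adjusted for sex, with hospital also accounted for. A Mantel-Haenszel test and Mantel-Haenszel relative risk with 95% confidence interval would serve, and they tolerate small strata. A stratum with patients in only one arm contributes nothing.
3. Either stratify the list by hospital as well, or say in one sentence why not. Stratifying means about 12 small strata and a slightly larger overall arm difference (mean about 2.4 rather than 0.8 patients in the blocks-of-four simulation).

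The cost is a regenerated list and a few lines of text. Trial status places the start of recruitment at about publication. If it has already begun, item 2 can still be fixed before unblinding.
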